##### Project B

After describing the recovery time course, we aim to investigate longitudinal associations between motor impairments in terms of leg muscle synergies (i.e., FMA-LE) and ankle strength (i.e., ankle item of the MI-LE) serving as independent variables, and the DCA which is the dependent variable. First, we analyze the pattern of neurological recovery following these clinical scales by using similar methods as outlined above. Second, we will apply a recently discussed hybrid model (64) to investigate longitudinal associations over the first 12 weeks poststroke. This method has the advantage of disentangling the between- and within-subject effects of this relation.

The between-subjects covariate score is determined as the individual average value over time of the independent variables which reveals the association irrespective of the development over time. On the other hand, the within-subject covariate is calculated as the observed value at each time point minus the individual average (i.e., deviation score). By this, we can estimate whether longitudinal changes of the dependent and independent variables within a subject are associated, i.e., are increasing scores on the FMA-LE or MI-LE ankle item related to changes following the DCA. Similar covariates will be entered in the model and tested on significance.

For all statistical tests, the likelihood ratio test will be used to examine the need to enter random effects into the model and the Wald test will be used to obtain *P*-values for regression coefficients in the final model. A 2-tailed significance level of 0.05 will be used for all analyses.

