### Objectives

In the current manuscript, we describe an observational cohort study that aims to prospectively investigate the time course of recovery of quiet stance balance control in the first 12 weeks after a first-ever hemispheric stroke. The relatively low functional demands of this condition (as compared to perturbed stance or walking) enables us to describe the process of balance skill re-acquisition even in more-severely impaired subjects and in the time window of spontaneous neurological recovery. Simultaneously, we will clinically observe the time course of recovery of lower limb motor impairments to investigate longitudinal associations with this leg's contribution to balance control.

The pre-defined research questions and hypotheses are:

What is the time course of recovery in the first 12 weeks poststroke in terms of balance control (a-)symmetries and overall stability during quiet stance? (i.e., project A).

First, we hypothesize that improvements in balance control symmetries toward values seen in healthy controls, as assessed through bilateral posturography (i.e., between-limb synchronization and contribution measures of corrective COP movements), are restricted to the first 5 weeks poststroke. Second, we hypothesize that an improved ability to maintain a stable standing position following traditional posturographic measures of body sway (i.e., stance stability) may develop beyond the time window and up until 12 weeks poststroke. As such, these later changes are hypothesized to reflect compensatory body stabilization exerted through the less-affected leg.

How are improvements in muscle synergies and ankle strength of the most-affected leg longitudinally associated with this leg's contribution to quiet stance balance control in the first 12 weeks poststroke? (i.e., project B).

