First, we hypothesize that clinical improvements in muscle synergies (i.e., Fugl-Meyer Motor Assessment) and strength (i.e., Motricity Index) at the hemiplegic side are mainly seen within the first 5 weeks poststroke, in accordance with previous longitudinal studies investigating time-dependent change (20, 23). Second, we hypothesize to find within this time window longitudinal associations between recovery on these scales and improved between-limb symmetry in balance control. This means that clinically observed improvements in motor impairments relate over the first weeks to an improved ability of this leg to contribute to corrective COP movements while standing quietly.

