#### Statistical Analysis

##### Project A

In project A, we aim to investigate time-dependent changes in metrics of quiet stance balance control. To estimate how each parameter is changing as a function of time poststroke, we use a random coefficient analysis (or mixed model analysis) with “time” of measurements as the main fixed effect (JMP Pro, version 15). Additionally, “time” will be entered as an independent covariate in form of an subject-specific slope (i.e., the interaction term “participant^*^time”) to adjust for dependency of repeated observations. However, the greatest advantage of this method is its flexibility in dealing with missing values. The latter may result from subjects being unable to stand at first occasions, being unavailable due to hospital discharge or transfers, or by no longer corresponding to eligibility criteria for example due to a recurrent stroke or other sudden medical condition (potentially) affecting outcome variables. Moreover, the value on the addressed metric at 3 weeks poststroke will be added to account for inter-subjects variability.

In addition, fixed covariates that are hypothesized to be potential confounders will be entered in the model. This includes “gender,” “age” and “BMI” considering their influence on standing balance control. [i.e., females and elderly tend to show greater body sway (60) and obesity is associated with instability (61)]. Second, stroke “side” and “type” will be added, as right-sided lesions typically result in greater balance deficits (62) and subjects with hemorrhagic strokes may display delayed recovery (63). Lastly, “equipment” is added as a potential confounder considering technical variations in measuring instruments.

Statistical analysis of the difference in each measure of quiet stance balance control between subjects and healthy controls will be performed using the Mann-Whitney U test for each measuring system separately.

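### Project B hypothesises an association within the first 5 weeks, but its single within-subject coefficient is pooled over 12 weeks and cannot show when the association occurs; whether time enters the model also needs stating

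*Protocol article*

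**What the plan says.** Under Objectives, the Project B research question asks how improvements in synergies and ankle strength are "longitudinally associated with this leg's contribution to quiet stance balance control in the first 12 weeks poststroke". The first Project B hypothesis expects clinical improvements that "are mainly seen within the first 5 weeks poststroke, in accordance with previous longitudinal studies investigating time-dependent change". The second builds on that window: "we hypothesize to find within this time window longitudinal associations between recovery on these scales and improved between-limb symmetry in balance control".

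Under Statistical Analysis, Project B, the association analysis covers the whole period: "we will apply a recently discussed hybrid model (64) to investigate longitudinal associations over the first 12 weeks poststroke". The dependent variable is dynamic control asymmetry (DCA). The predictors are the FMA-LE and the ankle item of the MI-LE. Each predictor is split into an individual mean over time and a deviation: "the within-subject covariate is calculated as the observed value at each time point minus the individual average (i.e., deviation score". From this, the article says, "we can estimate whether longitudinal changes of the dependent and independent variables within a subject are associated". The remaining terms are described in one sentence: "Similar covariates will be entered in the model and tested on significance". No split by period and no separate estimate for weeks 3 to 5 is described.

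For Project A, by contrast, time is named explicitly, "of measurements as the main fixed effect (JMP Pro, version 15", and again as a subject-specific slope.

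**The concern.** The window carries the study's interpretation. Early change in symmetry is to be read as restitution through the most-affected leg, and later change as compensation through the other. A hypothesis about weeks 3 to 5 needs an estimate that belongs to weeks 3 to 5. The planned coefficient averages over all four visits, only two of which lie in the window. A significant result could therefore be reported as support for an early association when the data hold only a late one.

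The second issue concerns what the coefficient measures. Impairment and symmetry are both expected to improve on average over the same weeks. If the model has no term for time, deviation scores on the two measures can correlate through the common curve, even if patients who gain more on the FMA-LE do not gain more symmetry.

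**Working it through.** The article gives no expected gains, SDs or power for this association, so there is no planned figure to reproduce. The gains, SDs, slopes and missing-data rates below are assumptions. From the article come the visits (weeks 3, 5, 8, 12), the two-sided 0.05 level and 60 × (1 − 0.15) = 51 completers.

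**1. What the pooled coefficient averages.** Let a patient's FMA-LE gains be *a* (weeks 3–5), *c* (5–8) and *d* (8–12). Over four complete visits, each gain enters as a step. After subtracting the patient mean, the sums of squares of the three steps are 0.75, 1 and 0.75. Their cross-products are 0.5 (*a*,*c*), 0.25 (*a*,*d*) and 0.5 (*c*,*d*).

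Assume independent gains with means 3, 2 and 1 and SD 2 each. Then E[a²] = 9 + 4 = 13, E[c²] = 8, E[d²] = 5, E[ac] = 6, E[ad] = 3, E[cd] = 2.

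- Total: 13×0.75 + 8×1 + 5×0.75 + 2×(6×0.5 + 3×0.25 + 2×0.5) = 31.0
- Early part: 13×0.75 + 6×0.5 + 3×0.25 = 13.5
- Early weight: 13.5/31.0 = 0.44; late weight: 0.56

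So the pooled slope is 0.44 × (early slope) + 0.56 × (late slope). With a true slope of −0.03 DCA per point in one window only, its expected value is about −0.013 (early only) or −0.017 (late only). Simulation with 51 patients and visit-level DCA SD 0.15 (600 runs) gave a significant coefficient in 92% and 98% of runs respectively.

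**2. A main effect of time does not cure this.** With visit as a factor, only between-patient spread in gains counts: total 4×(0.75 + 1 + 0.75) = 10, early part 4×0.75 = 3, early weight 0.30. The same simulation gave 29% significant for the early-only link and 87% for the late-only link.

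**3. Other assumptions.** Take gains of 3 (SD 2), 0.7 and 0.3 (SD 1.2 each), slope −0.04 and 45 patients. The total is 9.75 + 1.93 + 1.1475 + 2×(1.05 + 0.225 + 0.105) = 15.59, the early part is 9.75 + 1.05 + 0.225 = 11.03, and the early weight is 0.71. An early-only link is diluted from −0.04 to −0.028. At DCA SD 0.10, pooled rejection was 100% for an early-only link and 83% for a late-only link. The late-only figure fell to 55% at SD 0.15 and 35% at SD 0.20. At SD 0.10, change-on-change regressions by window separated the cases: 95% (weeks 3–5) against 5% (weeks 5–12) for the early-only link, and 6% against 85% for the late-only link.

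**4. Shared recovery if time is left out.** Assume no patient-level link. The common curve takes the fractions 0, 0.6, 0.9 and 1 of total gain, so the squared deviations sum to 0.6075. Mean FMA-LE gain is 6 (SD 3) with visit noise SD 1.5; DCA gain SD is 0.10 with visit noise SD 0.15. For a mean DCA change of −0.10:

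- Within-patient sum of squares of FMA-LE: (36 + 9)×0.6075 + 3×1.5² = 34.09
- Cross-product: 6×(−0.10)×0.6075 = −0.3645
- Expected coefficient: −0.3645/34.09 = −0.0107
- Within-patient sum of squares of DCA: (0.01 + 0.01)×0.6075 + 3×0.0225 = 0.0797
- Residual variance: 51×(0.0797 − 0.0107×0.3645)/152 = 0.0254
- SE: √(0.0254/(51×34.09)) = 0.0038; ratio 2.80; P(Z > 1.96 − 2.80) ≈ 0.80

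Simulation agrees:

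| Mean DCA change | No time term | No time term, 40% missing at week 3 and 20% at week 5 | Linear time | Visit as factor |
|---|---|---|---|---|
| 0 | 6% | 6% | 7% | 6% |
| 0.05 | 31% | 24% | 8% | 7% |
| 0.10 | 80% | 61% | 16% | 7% |
| 0.20 | 100% | 99% | 40% | 6% |

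The last two columns are without missing visits.

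**The case against.** Several counter-arguments have force.

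- **The model fits the research question.** That question covers 12 weeks, and the pooled coefficient answers it. A reader might infer that the hybrid model is wrong for Project B as a whole. The documents do not support that: the mismatch is with the second hypothesis only.
- **Time may be in the model.** A reader might infer that time is excluded. The article never says so. The sentence on similar covariates most naturally points to gender, age, BMI, lesion side and type, and equipment, but the Project A section itself calls time a covariate. A condensed article may leave the full list of terms to another document. This part is therefore a request for clarity. The window problem does not depend on it, as step 2 shows.
- **Shared recovery is part of the subject.** The article treats spontaneous neurological recovery as reflected by the passage of time. Removing the mean curve removes part of what is studied, so coefficients with and without time answer different questions. This stands, and it is a reason to report both.
- **Timing is partly analysed elsewhere.** The time courses of DCA and of the clinical scales are each modelled. That shows when each measure changes, but not when they are associated.
- **The percentages rest on assumed inputs.** This is true. The article's own Discussion notes earlier evidence that DCA changes little during inpatient rehabilitation. With a mean change of 0.02, rejection without time was only 6–8% in a separate check.

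**Conclusion.** The point holds in a limited form and should be fixed before analysis. From the text alone, one within-subject coefficient pooled over four visits cannot establish that an association lies in the first 5 weeks, with or without a main effect of time. The weights of 0.44 early and 0.56 late depend on the assumed gains (0.71 and 0.29 in the second set). That the coefficient mixes the two windows does not depend on them.

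The shared-recovery problem is conditional: it arises only if time is left out, and its size follows the mean change in DCA. It is near nominal with no change and far above 5% with changes near 0.10 to 0.15 under the assumed SDs. The rejection rates show direction and rough size and are not forecasts for this cohort. For an exploratory cohort without a power calculation, this limits what can be concluded about one hypothesis; it does not undermine the study.

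**What to change.** 1. Keep the pooled hybrid model for the 12-week question.
2. Add an interaction of the deviation score with period, or regress change in DCA on change in FMA-LE and MI-LE ankle score separately for weeks 3–5 and 5–12. Name the 3-to-5-week coefficient as the one that assesses the second hypothesis. Week 5 bounds both periods, so define the periods explicitly.
3. State whether time enters the hybrid model. Report the within-subject coefficient with and without visit as a four-level factor, and describe the unadjusted one as including shared recovery over time. A linear term is not enough if recovery levels off, as the article expects.

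No new data are needed. The main cost is precision. Under the second set of assumptions, the week 3–5 change test detected an early-only link in 95% of runs at DCA SD 0.10, 68% at 0.15 and 42% at 0.20. With SD 0.20 and 40% missing at week 3, it fell to 29%. Change scores also restrict that estimate to patients able to stand at both week 3 and week 5, which should be stated when it is interpreted. A four-level factor adds three terms and the interaction one per predictor. These should be set against the limit of 3 to 4 main covariates under Sample Size Justification, and the plan should say which terms take priority.

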### Design

The current recovery study is a non-interventional observational study meaning that no systematic interventions are applied next to usual care. For the duration of inpatient rehabilitation, this consists of 30- to 60-min sessions of physical and occupational therapy each workday following local guidelines.

After eligible subjects are included within the first 3 weeks poststroke, serial measurements will be scheduled at 3, 5, 8, and 12 weeks poststroke. Clinical evaluations are performed by the same assessor for each participant to decrease the effect of inter-rater variability when measuring within-subject change. In total, two physical therapists are available for clinical testing who underwent a training period to standardize assessment procedures prior to the study start. As soon as subjects are able to stand independently barefoot over at least 30 seconds, bilateral posturography will be performed during a standardized quiet stance task. For this purpose, either two separate force-plates (Type OR 6-7, AMTI, MA, US; measurement frequency 1 kHz) arranged in a side-by-side configuration as part of a stationary movement analysis laboratory (*M*^2^*OCEAN*, University Hospital Antwerp, Edegem, Belgium) or a portable pressure-plate system (0.5 m footscan 3D, RS Scan, Belgium; measurement frequency 500 Hz) will be used. This provides the advantage of executing this study in multiple (clinical) settings to facilitate recruitment and continuous data acquisition. Importantly, repeated within-subject measurements are always performed with the same equipment and these measurements are performed by a trained physiotherapist who is educated in using the measuring instruments.

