**Independent variables: Body functions level-Lower limb motor impairments**					
Fugl Meyer assessment–lower extremity		X	X	X	X
Motricity Index–lower extremity		X	X	X	X

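### Project B's individual average is not limited to occasions with a DCA value, so the within-subject coefficient can be biased in either direction

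*Protocol article*

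**What the plan says.** The Project B section names FMA-LE and the MI-LE ankle item as predictors, "serving as independent variables, and the DCA which is the dependent variable". It builds two covariates from each predictor. For the first, "The between-subjects covariate score is determined as the individual average value over time of the independent variables". For the second, "the within-subject covariate is calculated as the observed value at each time point minus the individual average". The section gives the separation of the two effects as the reason for choosing the hybrid model. It does not restrict the average to occasions that have an outcome value.

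Under Design, "serial measurements will be scheduled at 3, 5, 8, and 12 weeks poststroke". Table 1 marks FMA-LE and MI-LE at all four occasions, with no condition on standing. Table 1 also marks DCA at all four, but Design makes posturography conditional: "As soon as subjects are able to stand independently barefoot over at least 30 seconds, bilateral posturography will be performed". The Project A section expects missing outcome values for this reason: "The latter may result from subjects being unable to stand at first occasions".

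**The concern.** For a patient who cannot yet stand at week 3 or week 5, the clinical scores exist and the DCA does not. If the average uses every clinical score, it includes visits that never enter the regression. A deviation score isolates within-patient change only when it is centred on the rows that are analysed. Otherwise its mean within a patient is not zero, and that mean marks how late the patient stood and how much the score rose before standing.

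The within-subject coefficient is Project B's main answer: whether gains in synergy control or ankle strength go together with a changing contribution of the affected leg. If it carries a between-patient component, the separation claimed for the method is not assured.

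**Working it through.** **Inputs.** From the protocol: visits at 3, 5, 8 and 12 weeks; clinical scales at all four; DCA from first independent standing; n = 60. The protocol gives no slope, no standard deviations, no share of late standers and no link between standing date and DCA. Its sample size rests on recruitment and drop-out rates and a rule of thumb, so there is no figure on this point to reproduce. The scores and simulation inputs below are assumptions.

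**Step 1: one patient.** Assume FMA-LE scores of 10, 16, 20 and 22, with first standing at week 8.
- All-occasion mean: (10 + 16 + 20 + 22)/4 = 17. Analysed deviations: 20 − 17 = +3 and 22 − 17 = +5, sum +8.
- Mean over occasions with DCA: (20 + 22)/2 = 21. Deviations: −1 and +1, sum 0.
- The two centrings differ by a patient constant c = 21 − 17 = 4.

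**Step 2: algebra.** Let m_A be the all-occasion mean, m_O the mean over occasions with DCA, and c = m_O − m_A. Then c is zero for a patient measured at all four visits. It is positive for a late stander whose score rose before standing, and near zero for a late stander whose score stayed flat. Suppose

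DCA = a + bB·m_O + bW·(x − m_O) + u + e.

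Putting m_O = m_A + c gives

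DCA = a + bB·m_A + bW·(x − m_A) + (bB − bW)·c + u + e.

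A model with m_A and x − m_A leaves (bB − bW)·c + u at patient level. The within coefficient is unbiased only if that remainder is unrelated to c given m_A. With matched centring, the deviations sum to zero in each patient. They are then orthogonal to anything constant within a patient, and the weighting of a random-intercept model does not change this.

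**Step 3: size without a time term.** Random-intercept hybrid model, 40,000 simulated patients. Assumed: true within slope −0.030 DCA per FMA-LE point, intercept SD 0.10 or 0.25, residual SD 0.15, 38-48% late standers, 18-25% never standing.

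| Assumed patient-level structure | All-occasion mean |
|---|---|
| Standing date depends only on FMA-LE or is random; patient intercept linear in the four-occasion mean | −0.030 |
| Late standers more asymmetric than their mean score predicts | −0.0260 to −0.0266 |
| Late standers less asymmetric than their mean score predicts | −0.0332 to −0.0343 |
| Patient intercept tied to week-3 score, week-12 score, observed-occasion mean or late standing | −0.0276 to −0.0330 |

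Matched centring returned −0.030 in all of these, to within simulation noise.
- Row 2: 0.0034/0.030 = 11% to 0.0040/0.030 = 13% too small.
- Row 3: 0.0032/0.030 = 11% to 0.0043/0.030 = 14% too large.
- Row 4: up to 0.0030/0.030 = 10%, either sign.

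A separate simulation, also on assumed inputs, gave 12-15% too small and 10-13% too large for the situations in rows 2 and 3.

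At n = 60 (1,000 replicates) the all-occasion means were about −0.030, −0.026 and −0.034 for the first three rows. The sampling SD was about 0.0048, and 0.0048/0.030 = 16% of the slope. At this assumed slope every replicate was significant under either centring.

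**Step 4: with a time term.** With raw weeks added, matched centring gave −0.0183 to −0.0421, that is (0.030 − 0.0183)/0.030 = 39% too small to (0.0421 − 0.030)/0.030 = 40% too large. In the row 2 and row 3 scenarios, all-occasion centring with raw time gave −0.0254 to −0.0346, so matching the score alone could do worse. The reason is that late standers' rows sit at later weeks, so raw time itself carries a between-patient part. Splitting time over the same rows removes this by the argument in step 2.

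Random slopes and ceiling effects of the scales were not modelled.

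**The case against.** **The wording fits both implementations.** The article does not say whether rows without DCA are dropped before averaging. Such a choice is often left to an analysis plan, and the cited source for the hybrid model may settle it. It is true that all-occasion averaging is a reading and not an explicit statement. But the article does fix the rule, defines it on the predictors' own values, and attaches no condition on the outcome. An analyst following the text would include all clinical scores.

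**A reader might infer that the bias runs towards zero** and could hide a real association, because late standers should have worse DCA. The documents do not support this. It needs late standers to be more asymmetric than their average score already predicts, and nothing in the protocol says so. The protocol's own account of compensation makes the opposite possible: patients who rely on the less-affected leg may stand early and be more asymmetric. The Discussion also calls the cross-sectional relation between FMA-LE and control asymmetry weak, so the scores leave much asymmetry unexplained, in either direction.

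**The effect may be small.** The Introduction notes that some severely affected patients show no neurological recovery. Their scores stay flat, c is near zero, and little leaks. The simulated biases are also below one sampling SD. Both points stand, and they limit the size without removing the defect.

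**Matching has a price.** Averages of late standers would cover later weeks only, and matching alone fails if raw time is in the model. Both points are right, and the fix has to deal with them.

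**Conclusion.** The point holds as a conditional one. As written, the rule lets the occasions used for centring differ from the occasions analysed, and the protocol itself expects patients for whom they differ. The within-subject coefficient is then not guaranteed to be free of between-patient differences.

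In the assumed scenarios where standing date carries information about asymmetry beyond the mean score, the bias was roughly 10-15% of the slope in either direction. It was smaller in the other structures tried, and absent when standing date is unrelated to DCA given the scores. These figures rest wholly on assumed inputs and are not bounds. The documents settle neither sign nor size, and they do not support a claim that the plan will attenuate the association or miss it. The change is still worth making before analysis, because it concerns Project B's main coefficient and needs no new data.

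**What to change.** State in Project B that each patient's average and deviation scores are computed only from occasions with both a valid DCA and the clinical score concerned. The deviations then sum to zero within each patient over the analysed rows. If time enters the hybrid model, split it over the same rows into the patient's mean time and the deviation from it. The same applies to BMI if it is entered as a time-varying covariate.

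Costs: the between-subject average of late standers then covers later weeks only, so it is less comparable across patients. Patients with a single valid DCA inform only the between-subject coefficient; they hold no information on within-patient change. The all-occasion average can be reported as a sensitivity analysis, with the number of patients by first standing occasion, so that readers can see how far the two centrings differ. Otherwise the change takes a few sentences and a small amount of code.
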